**Criteria for Physical Therapists and Therapy Centers**	
**Inclusion Criteria**	**Exclusion Criteria**
Bachelor of Science in Physical Therapy for Swiss physical therapists and Master of Science in Physical therapy for Belgian physical therapists	Treatment centers only having open treatment rooms, which cannot guarantee privacy and treatment blinding
Fluent English and German or Dutch speaker	
Participation and completion of the trainings provided by the study personnel	
Availability of at least 1 therapist for the experimental and 1 for the control group per treatment location Hospital or private practice setting Treatment rooms that can be closed Similar equipment among the locations/treatment rooms Flexible treatment schedules of physical therapists to guarantee the blinding of participants (eg, no parallel sessions causing participants to see each other in the waiting room)	

^a^
Abbreviations: BMI = Body Mass Index (kg m^−2^); CNLBP = chronic non-specific low back pain; LBP = low back pain; NIH = National Institutes of Health; NPRS = numeric rating scale for pain (0 to 10); WHR = waist-to-hip ratio.

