### Randomization and Blinding

Patients will be randomly assigned to either the experimental or control group, utilizing a computer-generated number sequence. Randomization is stratified for weight category (overweight/obesity), sex (female/male), country (Belgium/Switzerland), and therapy center. The randomization lists with patient numbers and group allocation will only be accessible by an independent researcher. This researcher coordinates all appointment times with the therapist and assessors in both countries to avoid contact between assessors and therapists, assuring assessors’ blinding. In addition, the participants and the statistician will be blinded for allocation. For participants, this is possible as only a vague description of the therapy is provided in the ICF. Moreover, the therapists providing the experimental treatment are not involved in providing the control intervention and vice versa. The interventions will take place at different times during the day to avoid contamination between groups, and patients will not see each other at the hospital or private practice waiting rooms, nor at the university for measurements. Furthermore, blinding success for both patients and assessors will be evaluated by asking whether they believe the patient received the experimental or control intervention, along with their level of certainty (0% being very unsure, 100% being absolutely sure about the group assignment).

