#### Training of Therapists

All sessions will be provided by specially trained physical therapists. The training of PNE and CTET will be provided to all therapists, but only experimental therapists received the BWRP training to avoid treatment contamination. Therapists will not be allowed to switch groups after the training, but the content of the BWRP will be available for the control therapists at the end of the trial. The participants will be treated by the same physical therapist during the whole 14-week period. The training of the therapists will follow standardized intervention manuals (see Supplementary Material 4).

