### Statistical Analysis

#### Sample Size Calculation

A priori sample size calculation for the primary outcome (ie, pain intensity) was performed in GPower version 3.1.9.2 showed that a total sample size of 252 participants (126 in each country) is needed to achieve 95% power to detect a small effect size (partial *η*^2^ = 0.02), using a linear mixed model with alpha level .05 considering a 25% drop-out rate across 12 months of follow-up. Although the effect sizes for the primary outcome measure pain intensity in the proof-of-concept studies were medium to large^13^^,^^25–27^^,^^29^ we anticipate a smaller effect size in the present research proposal (partial *η*^2^ around 0.02), considering the fact that the control intervention has already been shown to be effective in reducing pain.^13^ Taking into account the drop-out rates in the proof of concept studies (9% to 23%),^13^^,^^26^^,^^27^ and the fact that the current proposal combines a weight reduction program with education plus exercise therapy, we anticipate a relatively higher drop-out rate of 25%. Allocation ratio (N2/N1) was defined as 1, resulting in 63 patients in each treatment group per country. A previous trial investigating the effectiveness of a healthy lifestyle intervention for patients with CLBP reported a sample size calculation of 80 participants, accounting for 15% loss to follow-up.^68^ This sample size provided 90% power to detect a clinical meaningful difference in pain intensity of 1.5 points on the Numeric Pain Rating Scale as primary outcome and 80% power to detect a 6% reduction in body weight as a secondary outcome. Based on the small effect size (partial *η*^2^ = 0.02), statistical analyses of other secondary outcome measures in this study should be adequately powered with a sample size of 252 participants.

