#### Statistical Analysis Plan

Prior to the analyses, visual inspection for assessing data plausibility will be performed, while the normality assumption will be checked using Q-Q-plots**.** Missing values will be checked for randomness by performing a logistic regression analysis, modeling the probability of missingness against baseline characteristics. If no significant associations are found, missingness will be assumed to be at random**.** Independent samples *t*-tests (for continuous variables) and chi-square tests (for categorical variables) will be performed at baseline to check whether the randomization was successful. If not, variables for which this was not the case will be included as confounders in the main analyses after the direction of the relationship was established using directed acyclic graphs (DAGs).^69^ Drop-out analysis will be performed using independent samples *t*-tests and chi-square tests on the baseline data, while the amount of and reasons for drop-out (participants are asked to give their reasons of withdrawal) will be compared between the experimental and control condition. This procedure will allow us to check whether differential drop-out (and thus attrition bias) is present. Again, variables subject to selection bias will be included as confounders (when identified as such by the DAGs) in the main analyses. General(ized) linear mixed modelling will be performed in R (RStudio version 1.1.383) to evaluate and compare (long-term) therapy effects between the experimental and control intervention. Both the distribution of the outcome measure and residual distributions will be checked for normality using Q-Q-plots. To account for clustering effects (ie, participants will be measured repeatedly, clustered within different hospitals or therapeutic settings), a multilevel model will be constructed, including three levels: (1) repeated measures, (2) clustered within the individual, and (3) clustered within a hospital or other therapeutic setting. This technique is particularly well fitted to analyze repeated measures over time in a hierarchical structure including missing values.^70^ To minimize issues related to multiple testing, contrast testing within the generalized linear mixed model framework will be applied. A priori defined contrasts between the groups will be tested using the R package “multcomp” and the function “glht.” Statistically significant differences will be defined at alpha level .05, and the effect size as well as clinically significant differences will be determined. In addition, numbers needed to treat will be calculated, after transforming the outcome to a binary variable, in analogy with previous research.^71^ Analyses will be performed based on the intention-to-treat principle. Afterward, per protocol analyses will be performed (as a form of sensitivity analysis) to evaluate the effect of therapy adherence and compliance.

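### Each therapist treats one arm only, but the planned model clusters on patient and centre; if therapists differ in their effect on 12-month pain, the standard error will be too small and the type I error above 5%

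*Protocol article*

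**What the plan says.** Four parts of the protocol article bear on this.

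- **Therapist and arm.** Under Randomization and Blinding, "the therapists providing the experimental treatment are not involved in providing the control intervention and vice versa". Training of Therapists adds that switching arms after training is not allowed.
- **Patient and therapist.** Training of Therapists: "The participants will be treated by the same physical therapist during the whole 14-week period".
- **Centre and arm.** Table 1 requires of each site "Availability of at least 1 therapist for the experimental and 1 for the control group per treatment location", and randomization is stratified by therapy center. Both arms therefore run at every location, with different therapists.
- **Model.** The Statistical Analysis Plan section sets out a three-level model to deal with clustering: repeated measures, then "2) clustered within the individual, and (3) clustered within a hospital or other therapeutic setting". On the error rate it says "Statistically significant differences will be defined at alpha level .05".

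The Sample Size Calculation section says that "a total sample size of 252 participants (126 in each country") "is needed to achieve 95% power to detect a small effect size". It allows for 25% drop-out but mentions no clustering.

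**The concern.** A clustering level protects the test of treatment only if it is the unit whose variation enters the treatment contrast. Centre is crossed with arm, so a centre effect is shared by both arms at a site and cancels in the within-site comparison. Therapist is nested in centre and arm, so differences between therapists remain in the comparison. The listed levels contain the first unit and omit the second.

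At stake is the primary test. Treatment is largely one-on-one, and the article's limitations note that the physical therapists have no established experience in delivering the weight programme, so some variation between therapists is plausible. Any such variation would be counted as if it were independent patient-level noise. The interval for the 12-month effect would then be too narrow, and a chance difference between two small sets of therapists could be declared significant.

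**Working it through.** **1. The plan's own sample size.** Inputs from Sample Size Calculation: partial η² = 0.02, alpha .05, 95% power, 25% drop-out. Pain is measured at five visits (T0, T1, T2, T3, T5). Assumed, because not stated: repeated-measures ANOVA with group-by-time interaction, correlation 0.5, sphericity.

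- f² = 0.02/0.98 = 0.0204.
- λ = f²·N·5/(1 − 0.5). N = 94 gives λ = 19.2 and 95% power.
- 94/0.75 = 125.3, rounded up to 126, the stated number per country; two countries give 252.

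The figure is reproduced with no term for clustering. Completers: 252 × 0.75 = 189.

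**2. Which variance enters the contrast.** Write the pain change of a patient in centre c with therapist t as arm effect + centre effect + therapist effect + patient error. Subtracting arms within a centre removes the centre effect and leaves the difference of two therapist effects. With k therapists per arm and m patients each:

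- true variance of the contrast = 2(m·σ²t + σ²e)/(k·m)
- variance used when therapist is omitted ≈ 2(σ²t + σ²e)/(k·m)
- ratio = design effect DE = 1 + (m − 1)·ICC, with ICC = σ²t/(σ²t + σ²e)
- actual type I error ≈ 2·[1 − Φ(1.96/√DE)]

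**3. Numbers.** Therapist counts and ICCs are assumptions. With 189 completers and equal loads, m = 189/(2k): 15.75, 9.45 and 4.73 for k = 6, 10 and 20. For k = 10 and ICC 0.05, DE = 1 + 8.45 × 0.05 = 1.42, √DE = 1.19, 1.96/1.19 = 1.64, so the type I error is 10.0%.

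The simulated values fit a centre-random-intercept model to a 12-month endpoint under no treatment effect, with one therapist per arm per centre and 2,000 runs per cell. Each cell shows formula / simulation.

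| Therapists per arm | ICC 0 (simulation) | ICC 0.01 | ICC 0.02 | ICC 0.05 | ICC 0.10 |
|---|---|---|---|---|---|
| 6 | 6.0% | 6.7 / 7.3% | 8.5 / 7.9% | 13.7 / 15.7% | 21.3 / 22.7% |
| 10 | 4.7% | 6.0 / 5.1% | 7.0 / 7.5% | 10.0 / 9.8% | 14.9 / 15.5% |
| 20 | 5.2% | 5.4 / 5.5% | 5.9 / 6.9% | 7.2 / 7.2% | 9.4 / 10.1% |

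Monte Carlo standard error near 5% is √(0.05 × 0.95/2000) ≈ 0.5 points, so the ICC 0.01 cells can barely be told from nominal.

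**4. Longitudinal check.** Five visits, patient and centre intercepts, T0-to-T5 arm contrast, therapist effect on post-baseline visits only, about 190 completers, within-patient correlation 0.5, 4,000 runs. For 6, 10 and 20 centres (one therapist per arm in each), the type I error is 9.3%, 7.5% and 6.5% at ICC 0.02, and 14.1%, 12.0% and 8.3% at ICC 0.05. The repeated measures do not remove the problem.

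**5. After the fix.** Testing the 12-month endpoint of step 3 against therapist (centre-by-arm) variation rejected in 4.4–5.9% of runs across all ICCs from 0 to 0.10.

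**6. Power.** Take a single contrast with exactly 95% power without clustering. Its expected z is 1.96 + 1.645 = 3.605. With valid errors, power is Φ(3.605/√DE − 1.96). At ICC 0.05, DE is 1.74, 1.42 and 1.19 for 6, 10 and 20 therapists per arm, giving about 78%, 86% and 91%, before any loss of degrees of freedom. At DE 1.42, 189 completers carry the information of 189/1.42 ≈ 133.

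**The case against.** The strongest reply is that the size is unknown and may be small. The article gives no ICC, no therapist count and no centre count. The endpoint comes at 12 months, after a 14-week treatment, with other care permitted in between. Manuals, training, fidelity scoring and refresher courses should make therapists more alike. One therapist per arm per site is only the required minimum; more would mean smaller clusters. All of this stands: it makes the claim conditional and argues against resting it on scenarios with very few centres. None of it shows the ICC to be zero.

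A second reply is that the article fixes levels, not the random-effects structure, so a random treatment slope at centre level could carry the therapist variance. It could, with one therapist per arm per site, but no such slope is stated. Nor can the third level be read as therapist, since each location must house therapists of both arms.

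A reader might also infer that therapist skill is confounded with arm and biases the estimate. The documents do not support that. Nothing suggests that better therapists are placed in one arm, and therapist differences average out over the therapists in each arm. The fault is an understated variance, not a systematic shift.

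**Conclusion.** The point holds in conditional form. The structure comes directly from the text: therapist nested in centre and arm, centre crossed with arm, and a stated list of levels without therapist. This is more than detail left to a fuller analysis plan, because the article names its clustering levels and they do not match its own account of delivery.

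If the therapist ICC for 12-month pain is above zero, the type I error will exceed 5%. For 189 completers, equal loads and 6–20 therapists per arm it is about 5–7% at ICC 0.01, 7–8% at 0.02, 7–16% at 0.05 and 10–23% at 0.10. These are scenarios, not estimates of this trial's error rate. A reader might conclude that the test is certainly anti-conservative, or that a particular inflation applies. The article supports neither, because it supplies no ICC or therapist numbers, and at ICC zero the planned test keeps about 5%.

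**What to change.** - **Model.** Add a random effect for therapist, nested in centre and arm, or a centre-by-arm random effect. Let it act on the post-baseline scores, for example with baseline pain as covariate and a therapist random intercept. If T0 is kept as an outcome, a therapist intercept common to all visits would cancel in the change from baseline and would not help. Keep centre in the model.
- **Inference.** Use Satterthwaite or Kenward-Roger degrees of freedom, since therapists may be few.
- **Sample-size text.** Say that 95% power assumes no therapist clustering, and give the design effect over a range of assumed ICCs and the actual number of therapists.

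No extra participants and no change in conduct are needed. The analysis dataset must carry a therapist code. Because therapist determines arm, the codes must be masked so that the statistician stays blinded. If the ICC is above zero, confidence intervals widen and effective power falls, as in step 6 of the working. With 79 patients included when the article was written, the change can be made before analysis.

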**Conclusion:**

This study is the first international multicenter RCT integrating a lifestyle approach into evidence-based physical therapy for people with CNLBP and comorbid overweight or obesity. It will assess whether addressing comorbid overweight or obesity enhances pain reduction and other health outcomes in this population.

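### Contrast testing inside each outcome's model is the stated answer to multiple testing, but it does not control error across the 19 to 21 secondary outcomes, for which .05 is the only threshold

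*Protocol article*

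**What the plan says.** The Statistical Analysis Plan section states the multiplicity measure in one sentence: "To minimize issues related to multiple testing, contrast testing within the generalized linear mixed model framework will be applied". It continues: "A priori defined contrasts between the groups will be tested using the R package" multcomp, with the function glht. No adjustment method is named. The threshold follows, without distinguishing primary from secondary outcomes: "Statistically significant differences will be defined at alpha level .05, and the effect size as well as clinically significant differences will be determined".

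The Primary Outcomes section fixes one primary endpoint, the between-group difference in change in average pain intensity from baseline to 12 months. The Introduction lists six secondary objectives, and Table 2 gives the outcomes under them. The Sample Size Calculation, after sizing the trial on pain intensity, adds that "statistical analyses of other secondary outcome measures in this study should be adequately powered with a sample size of 252 participants". The Conclusion of the abstract says of the trial: "It will assess whether addressing comorbid overweight or obesity enhances pain reduction and other health outcomes in this population". Nowhere does the article rank the secondary outcomes or call them exploratory.

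The last paragraph of the Statistical Analysis Plan section sends costs to a health economic evaluation with cost-effectiveness and cost-utility planes and incremental ratios. It states no .05 test there.

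**The concern.** The remedy does not reach the whole problem that it is offered for. Each outcome has its own mixed model, and a set of contrasts in one model shares error control only within that model. Between pain interference, kinesiophobia, body fat, sleep, quality of life and the rest, nothing limits how often chance alone produces a p-value below .05.

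This would matter little if the secondary outcomes were plainly supportive. The article leaves that open. It calls them adequately powered, and it presents the trial as a test of effects on other health outcomes as well as pain. The abstract and Discussion expect the results to inform guidelines and policy. A reader of the final report could therefore take an isolated significant secondary result as an established effect, believing that multiplicity had been dealt with.

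**Working it through.** The article states no family-wise error rate, so there is no figure of its own to reproduce. The check counts the outcomes and computes the rate that the stated rule allows.

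**Inputs from the article**
- Threshold: .05 (Statistical Analysis Plan). Sidedness is not stated; two-sided is assumed, so .025 in the direction of benefit.
- Secondary outcomes measured after baseline (Table 2):
  - pain-related: 4 (pain distribution, pain interference, kinesiophobia, fear avoidance)
  - body composition: 9 (BMI, weight, body fat, fat free mass, waist, hip, waist-to-hip ratio, adipose tissue thickness, muscle thickness; height is baseline only)
  - energy balance: 5 (dietary intake, sleep quantity, sleep quality, rest-activity cycles, physical activity)
  - costs: 2
  - quality of life: 1
- Total: 4 + 9 + 5 + 2 + 1 = 21. Without costs: 21 − 2 = 19. Without body composition as well: 19 − 9 = 10.

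**Assumptions**
- One test per outcome, that is, the contrasts within each model are taken to be fully handled.
- All counted outcomes are truly null.
- Equal correlation ρ between test statistics. The article gives none, so 0 to 0.8 is shown.

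**Formulas**
- Independent tests, any direction: 1 − 0.95^m. Benefit direction: 1 − 0.975^m.
- Correlated tests, any direction: 1 − ∫ [Φ((1.96 − √ρ·u)/√(1−ρ)) − Φ((−1.96 − √ρ·u)/√(1−ρ))]^m φ(u) du. For the benefit direction, drop the second Φ term.

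**Numbers put in at ρ = 0**
- m = 19: 1 − 0.95^19 = 1 − 0.377 = 0.62; 1 − 0.975^19 = 1 − 0.618 = 0.38.
- m = 10: 1 − 0.95^10 = 1 − 0.599 = 0.40; 1 − 0.975^10 = 1 − 0.776 = 0.22.

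**Chance of at least one false significant result (ρ = 0 / 0.5 / 0.8)**

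| Null outcomes | Any direction (nominal .05) | Benefit direction (nominal .025) |
|---|---|---|
| 21 (all in Table 2) | 0.66 / 0.43 / 0.23 | 0.41 / 0.22 / 0.11 |
| 19 (costs left out) | 0.62 / 0.41 / 0.22 | 0.38 / 0.21 / 0.11 |
| 10 (costs left out, body-composition effects real) | 0.40 / 0.29 / 0.17 | 0.22 / 0.14 / 0.09 |

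The most favourable row and correlation still give 0.17/.05, about 3.5 times nominal. The 19-outcome row runs from 0.22/.05 = 4.4 to 0.62/.05 = 12.4 times nominal.

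**The case against.** **The primary claim is protected.** One item at one time point is fixed in advance, and everything else is labelled secondary. Unadjusted secondary analyses are common in that setting. This stands, and it limits the point to how the secondary results are read.

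**Details may be in a fuller plan.** A missing hierarchy or exploratory label would not on its own be a finding against a journal article. That is fair. But the article does state a measure and a threshold, and the measure as stated falls short of the problem it names. It claims only to minimize the problem, which softens the sentence but does not extend contrasts across models.

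**The family is smaller than 21.** Costs go to an economic evaluation, so a .05 test of them is an inference. A weight-reduction programme is meant to change body composition, so those nulls may be false. Both are accepted, which is why the 19- and 10-outcome rows are shown. In the other direction, counting one test per outcome is lenient: Table 3 describes two subscales for kinesiophobia and six sites for adipose tissue thickness.

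**Adequate power concerns missed effects, not false ones.** Correct. The sentence does not raise the error rate; it only invites readers to give secondary results confirmatory weight.

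**Stronger readings that a reader might infer.** One is that every outcome at every post-baseline visit is tested unadjusted, which would be 61 contrasts in Table 2 and a rate of up to 0.96. The text does not say this: it speaks of contrasts defined in advance, does not say that every visit is tested, and does not say that they are unadjusted. Independence across visits of one outcome, or between weight and BMI, is also implausible. The other is that a false benefit is likely; the benefit-direction figures do not support it.

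**Conclusion.** The point holds in limited form. The stated remedy controls error only among the contrasts of one outcome's model, and .05 is the only threshold for the secondary outcomes. For 19 null outcomes the chance of at least one false significant result is 0.62 to 0.22 over correlations of 0 to 0.8; for 10 it is 0.40 to 0.17. That is a substantial inflation under every assumption tried.

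It does not follow that the trial will probably report a false benefit. In that direction the rate is at most 0.41 with all 21 outcomes null and independent, and 0.21 for 19 outcomes at correlation 0.5. Nor does the point touch the 12-month pain-intensity test. The figures rest on assumed correlations, two-sided testing, one test per outcome and true nulls for the outcomes counted. The direction of the conclusion does not depend on which of these cases is chosen. The plan should be corrected, but the trial's main result is not threatened.

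**What to change.** In the Statistical Analysis Plan section:
- Say that contrast testing addresses comparisons within an outcome only.
- State that the 12-month pain-intensity contrast is the sole confirmatory test.
- State that secondary outcomes are supportive or exploratory, reported as estimates with 95% confidence intervals and not claimed as established effects.

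An optional alternative is a short list of key secondary outcomes, ordered in advance and tested in sequence at .05 only if the primary is significant, with the rest exploratory.

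In the Sample Size Calculation, drop or qualify the sentence on adequate power so that it does not give the secondary outcomes confirmatory weight.

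The cost is wording. No new data are needed and the primary test does not change. With 79 of 252 participants included when the article was written (Study Design), the status of the secondary outcomes can be settled before results are known. The downside is that the sponsor gives up confirmatory claims on most secondary outcomes.

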	Rest activity cycles	Fitbit Sense (wrist-worn activity monitor)	To capture continuous rest/activity cycles an accelerometry (Fitbit Sense 1 or 2, Fitbit International Limited, Dublin 2, Ireland) is used. This wrist-worn package will be installed 1 week prior to the treatment, will continue throughout the 14 weeks treatment, and will end the day of the follow-up body composition measurement (T1). Participants are instructed to wear the device constantly (day and night) and to synchronize the watch with the app once a day to ensure data storage. At T5, the last follow-up measurement, the Fitbit is handed out again and the participants are instructed to wear the accelerometer for 1 additional week.
	Sleep quality	Pittsburgh Sleep Quality Index (PSQI), Fitbit	The PSQI is a widely used tool to assess sleep quality.^63^^,^^64^ The PSQI is assessed using the REDCap software.
	Sleep quantity	Fitbit Sense	Sleep quantity and quality will be monitored using the Fitbit watch, including sleep schedules, time spent in bed, sleep duration, wake duration, and number of awakenings. While these devices are not recommended for diagnosing sleep disorders, they are suitable for monitoring sleep–wake behavior over extended periods.
	Continuous physical activity	Fitbit Sense	Continuous physical activity and rest/activity cycles are measured with an activity monitor (Fitbit Sense 1 or 2). Data analysis occurs through Fitabase software. Next to physical activity, sedentary behavior will be investigated with the accelerometer data.
Costs			
	Medical consumption	Medical Consumption Questionnaire (MCQ)	Medical consumption (including co-interventions) will be recorded using the Medical Consumption Questionnaire, which is a generic instrument for measuring patients’ total (in-)direct medical consumption.^38^ The MCQ is assessed using the REDCap software.
	Indirect health costs	Productivity Cost Questionnaire (PCQ)	The Productivity Cost Questionnaire will be used to obtain data regarding the indirect costs (eg, costs due to absenteeism or presenteeism).^65^ Costs will be reported in non-aggregated form and will be calculated as “units consumed × unit cost.” Unit costs will be extracted from country specific databases for health care services and drugs. All costs will be expressed in 2026 Belgium euro and for Swiss data also in 2026 Swiss Francs. Intangible costs (eg, pain, stigma) will be omitted. The PCQ is assessed using the REDCap software.
Quality of life			

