
For the health economic evaluation, cost-effectiveness and cost-utility planes will be created to illustrate the incremental values of costs and clinical outcomes including the results of a probabilistic sensitivity analysis. If neither of the 2 treatment groups is dominant, incremental cost-effectiveness ratios and incremental cost-utility ratios will be calculated. The analysis will be conducted separately per country and from both health care and societal perspective with a time horizon of 66 weeks.

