## DISCUSSION

This RCT will be the first sufficiently powered trial to investigate the efficacy and cost-effectiveness of adding a BWRP to best-evidence physical therapy (PNE plus CTET) in people with CNLBP and comorbid overweight or obesity in two different countries. Given the strong link between CLBP and overweight/obesity, as well as their detrimental bidirectional impact, this study will have the potential to significantly improve clinical care for people with CNLBP.

Despite the rise of medications facilitating weight loss, the cornerstone of obesity management in the United States, United Kingdom, and Europe lies in a multicomponent lifestyle intervention, including nutrition, exercise, and behavioral therapy.^77^^,^^78^ While anti-obesity medications are effective in supporting weight reduction, they are also associated with various side effects and adverse events that should not be underestimated.^77–82^ Moreover, access to these medications remains limited, not all patients are eligible to obtain them, and they are typically prescribed alongside mandatory lifestyle and dietary changes.^77^^,^^83^ Discontinuation of the pharmacotherapy results in an increase in body weight, indicating in a long-term dependency.^83^ Notably, combining physical activity with medication has been shown to improve healthy weight maintenance after treatment termination, compared to either intervention alone.^84^ Both Switzerland and Belgium follow a similar patient-centered, multidisciplinary approach as the first line of obesity treatment. In Switzerland, initial management includes dietary changes, increased physical activity, psychological support, and diabetes counseling when necessary.^85^^,^^86^ Only adults with a BMI ≥35 or a BMI ≥27 in combination with a comorbidity like high blood pressure may be eligible for anti-obesity medication.^85^^,^^86^ Similarly, in Belgium, policy recommendations emphasize treatments by a psychologist, dietician, and physical therapist, with anti-obesity medication considered as an optional component of treatment.^87^ This underscores the rationale for the planned RCT, which aims to evaluate the combined effects of PNE, CTET, and BWRP within a physical therapy setting in two countries.

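### The trial is called sufficiently powered for cost-effectiveness, but the sample size rests on pain intensity alone and the economic evaluation is described only per country, on half the sample each

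*Protocol article*

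**What the plan says.** Four places in the protocol article bear on this.

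- **Discussion, opening sentence:** "This RCT will be the first sufficiently powered trial to investigate the efficacy and cost-effectiveness" of adding the weight reduction programme. The power claim names cost-effectiveness expressly.
- **Sample Size Calculation:** "A priori sample size calculation for the primary outcome (ie, pain intensity) was performed in GPower", and the result is that "a total sample size of 252 participants (126 in each country) is needed to achieve 95% power" for a partial eta squared of 0.02. The section closes by saying that "statistical analyses of other secondary outcome measures in this study should be adequately powered with a sample size of 252 participants". The secondary objectives in the Introduction and the Secondary Outcomes section list medical consumption, indirect health costs and quality of life, so the inputs to the economic evaluation fall under that sentence.
- **Statistical Analysis Plan, last paragraph:** cost-effectiveness and cost-utility planes, a probabilistic sensitivity analysis and, where neither arm dominates, incremental ratios. Then: "The analysis will be conducted separately per country and from both health care and societal perspective", over 66 weeks.
- **Table 3, indirect health costs:** "All costs will be expressed in 2026 Belgium euro and for Swiss data also in 2026 Swiss Francs". Swiss costs will therefore also exist in the currency used for Belgium.

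The article gives no power or precision figure for costs, QALYs or cost-effectiveness, and mentions no pooled economic evaluation.

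**The concern.** The article asserts a property of the design, sufficient power for cost-effectiveness, that nothing in the design supplies. The sample size calculation has no cost or QALY input. The number for which adequacy is asserted, 252, is not the number on which the economic evaluation is described. That number is 126 per country.

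The stake is how the economic results will be read. The Discussion calls cost-effectiveness evaluation essential and the usual basis for taking up new treatments. If the two country evaluations are imprecise, or point in different directions, a reader who trusts the power statement will take that as the finding of a trial built to answer the question. The primary analysis of pain is not affected.

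**Working it through.** **Inputs.** From the Sample Size Calculation section: 252 in total, 126 per country, 63 per arm per country, 1:1 allocation, alpha .05 (sidedness not given; two-sided assumed), 95% power, partial eta squared 0.02, 25% drop-out. From the Primary Outcomes section: five pain assessments (T0, T1, T2, T3, T5).

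**The plan's own figure.** f² = 0.02/(1 − 0.02) = 0.0204, so f = 0.143. Take a repeated-measures group-by-time interaction with 2 groups and m = 5 measurements, noncentrality f²·N·m/(1 − ρ), and an assumed correlation ρ = 0.5 (not stated in the article). The smallest N with 95% power is 94, and 94/0.75 = 125.3, rounded up to 126. That equals the per-country figure, and 2 × 126 = 252. The article nevertheless presents 252 as the total needed, and another variant (four groups, five times, ρ = 0.3) gives 184, with 184/0.75 = 245.3, or 246, which is close to 252. Whether the calculation was made per country or overall therefore cannot be settled. On either reading it concerns a repeated pain score. A cost or QALY total gives one value per person, so this power does not carry over to it.

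**Sample available to the economic evaluation.** Per country: 126 × 0.75 = 94.5, about 47 per arm. Pooled: 252 × 0.75 = 189, about 94 per arm.

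**Illustration.** Assume a two-arm comparison of one value per person, roughly normal, without clustering or covariate adjustment. Assume also a standardised difference d = 2f = 0.286. This borrows the pain effect size; the documents give none for costs or QALYs.

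- Standard error of d: 2/√N
- Power: Φ(d/SE − 1.96)
- Difference detectable with 80% power: (1.96 + 0.84) × SE

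| Sample | N | SE | d/SE | Power | Detectable at 80% |
|---|---|---|---|---|---|
| One country, randomised | 126 | 0.178 | 1.60 | 36% | 0.50 SD |
| One country, after drop-out | 94 | 0.206 | 1.39 | 28% | 0.58 SD |
| Pooled, randomised | 252 | 0.126 | 2.27 | 62% | 0.35 SD |
| Pooled, after drop-out | 189 | 0.145 | 1.96 | 50% | 0.41 SD |

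**Precision, which needs no effect size.** The ratio of standard errors is √(252/126) = √2 = 1.41. After drop-out the 95% half-width is 1.96 × 0.206 = 0.40 SD per country against 1.96 × 0.145 = 0.28 SD pooled.

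**Result.** At this assumed difference neither the country samples nor the pooled sample reaches 80% power, let alone the 95% planned for pain. Pooling improves precision but does not by itself justify the power statement.

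**The case against.** The strongest reply is that evaluating each country separately is a legitimate choice. Unit costs come from country-specific databases, several national tariffs are planned for the utilities, and the plan is estimation (planes, probabilistic sensitivity analysis, incremental ratios) without a hypothesis test. That stands: the split is not in itself an error, and the power percentages describe a test that the plan does not contain. The borrowed effect size is open to the same reply. With d = 0.286 and one value per person, pain itself would need 638 evaluable participants, or 638/0.75 = 851 randomised. This is not the plan's own power framework, and the percentages serve only as illustration.

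A reader might go further than the documents allow in four ways.

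- **Pooling is ruled out.** It is not. The article is silent, and a fuller economic plan may exist. Such a plan could add a pooled estimate, but it could not supply a basis for the published power sentences as they stand.
- **The country evaluations would be the only economic evidence.** The mixed-model plan is not split by country and could cover costs and quality of life as secondary outcomes.
- **Nothing stands in the way of pooling.** A common currency is planned, but unit costs and tariffs still differ between the countries.
- **Cost-effectiveness is a main aim.** The primary objective is pain at 12 months. Medical consumption and indirect costs are two of six secondary objectives, although the Discussion stresses the economic case.

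None of this supplies a basis for the power statement. An estimation-based evaluation without a power calculation is acceptable, but it should not be called sufficiently powered.

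**Conclusion.** The point holds as an unsupported claim. The Discussion asserts sufficient power for cost-effectiveness, and the Sample Size Calculation section asserts it for secondary outcomes at 252. The calculation covers pain intensity only, and the economic evaluation is described on 126 per country. No basis is given at either number.

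The firm part of the size is the factor of 1.41 in standard errors between a country evaluation and a pooled one, which assumes similar variability in the two countries. The power figures after drop-out (about 28% against 50%) depend on the assumed difference of 0.286 and on approximate normality. Skewed costs would make precision worse.

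It would be tempting to conclude that the per-country split causes the problem and that pooling would cure it. The figures do not support this, because the pooled sample also falls short at that difference. The wording should be corrected; the pooled analysis is a low-cost gain in precision, not a repair of the claim.

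**What to change.** 1. **Sample Size Calculation and Discussion:** restrict the power statement to pain intensity. Describe the economic evaluation as estimation, reported with its uncertainty.
2. **Statistical Analysis Plan, economic paragraph:** keep the per-country evaluations. Add a supplementary pooled cost-effectiveness and cost-utility analysis of all randomised participants, with costs in 2026 euro, country as a covariate and the treatment-by-country term reported. State which tariff is used for the pooled utilities.

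The cost is small: reworded sentences in two places and one further analysis of data already being collected. The article reports 79 participants included at the time of writing, so the change can be made well before the results. The downside is that the pooled estimate averages over two health systems with different unit costs and tariffs. It should be read beside the country results and should not replace them.
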